**2.17.2 Serious adverse events (SAE)**

Four months after randomization of 25%, 50%, and 75% of subjects, interim analyses will be performed of SAE. The DSMB will consider stopping the trial early if SAE rates are significantly ***higher*** with 4RIF. To balance the risk of unnecessarily stopping the study with interim analyses 196, with the need to ensure patient safety, we will use the method of Pocock 197, or an interim stopping level (p value) of 0.018 for each analysis.

**2.18 Planned sub-group and secondary analyses:**

**2.18.1 Active TB in subjects who complete treatment (efficacy)**

Non-completion of therapy is obviously not a random event, and may be associated with characteristics that are associated with risk of disease166. Therefore we will compare the characteristics of compliant and noncompliant subjects in each group, and use logistic regression to estimate efficacy, adjusted for important covariates.

**2.18.2 Confirmed and probable active TB**

In secondary analysis we will combine these two outcomes, and use the same methods to compare rates of TB with both regimens, as described above for the primary analysis.

**2.18.3 SAE**

This outcome will be defined as the occurrence of Grade 3 or 4 SAE, diagnosed by the majority of the independent reviewers. Differences in all SAE, and by type of SAE between the two groups will be tested with Chi-squared or Fisher’s exact tests. Sub-group analyses will compare rates of SAE by age, sex and HIV status. Drug interactions with 4RIF are common, and of particular interest since this will be the largest trial with mono-Rifampin therapy. All analysis of SAE and drug interactions will be presented as exploratory, with appropriate caution 166, 196. However in view of the very limited published experience with 4RIF, any information about adverse effects, including drug interactions, would be very useful for clinicians.

**2.18.4 Drug resistance among cases of active TB after randomization**

The occurrence of drug resistant TB after LTBI therapy may result from selection of drug resistant mutants during therapy (acquired resistance), or because they were infected with drug resistant organisms (primary resistance). All patients with positive cultures for M Tuberculosis within 28 months after randomization will have drug sensitivity testing. Adequate facilities are available in all sites. If drug resistant tuberculosis is found, patients will be placed on appropriate therapy and followed by the site investigators in collaboration with the local TB programs. We will compare the prevalence of resistance to INH and RIF among study participants who develop active TB. The prevalence of underlying (or primary) INH resistance in the community will be assumed as the prevalence in those who took 4RIF, and of RIF resistance in those on 9INH. Acquired RIF resistance will be taken as the difference in prevalence of RIF resistance between subjects on 4RIF and 9INH. Power to detect significant differences will be limited, unless drug resistance is very common, but descriptive information on any excess resistance would still be useful.

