**1.6 Risks for the trial participants**

Available evidence, from *millions* of patients treated for active TB with RIF in combination with other drugs 154, 155, suggests that RIF is well tolerated and safe. Hepatitis is the most important and potentially fatal complication of INH and RIF-PZA therapy of LTBI. On the other hand, mono-therapy with RIF has been associated with very low rates of hepatitis – in Phase 1&2 131, 148, and elsewhere 33, 121-124 (RCT Appendix 1 - Table 5). Nevertheless, in view of the 2RIF-PZA experience, where initial trials suggested excellent safety, but unacceptable toxicity was seen with introduction into routine practice, it is prudent to continue to closely monitor the safety of 4RIF. This will be done by independent review of all possible Grade 3 or 4 SAE, plus periodic interim analyses of safety during the trial. Patients will be carefully questioned regarding concomitant medications, to identify potential drug interactions, and will be excluded if these can not be managed easily. Mono-therapy of patients with unrecognized active TB, of particular concern in HIV infected patients, may lead to drug resistance, which has serious implications for treatment152, 153. In all settings we will ensure that study participants have access to all necessary investigations to exclude active TB, including cultures. In some settings this means budgetary allocations to pay for these investigations if necessary. In the long term, 4RIF will not be useful in resource-limited settings if extensive investigations are needed before starting therapy. Hence, we will develop and evaluate low cost diagnostic algorithms to identify candidates for LTBI therapy likely to have active TB, for use after the trial (RCT Appendix 5). Initial or primary drug resistance can render LTBI therapy ineffective 127. However rates of RIF resistance rates are very low and much lower than INH resistance in all participating countries (RCT Appendix 1 - Table 6) 156, 157, enhancing the rationale and ethical acceptability of evaluating 4RIF. INH is recommended unless prevalence of primary drug resistance exceeds 50% 107, 158 - clearly not the case in any country, or if the subject is a contact of INH resistant cases INH 107, 138 – an exclusion criteria for this trial. Finally, subjects will be followed two full years after completing 4RIF to ensure early detection of active TB if this therapy fails.

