**2.5.2 Exclusion criteria**

1. Patients who were contacts of TB cases known to be resistant to INH, RIF, or both (i.e. MDR)107, 138,127.

2. Known HIV-infected individuals on anti-retroviral agents whose efficacy would be substantially reduced by Rifampin, unless therapy can safely be changed to agents not affected by Rifampin (listed in RCT quick guide - Appendix 5).

3. Pregnant women - Rifampin and INH are considered safe in pregnancy 138, 167, but therapy is usually deferred until 2-3 months post-partum to avoid fetal risk and the potential for increased hepato-toxicity immediately post partum 168.

4. Patient on any medication with clinically important drug interactions with INH or RIF, which their physician believes would make either arm contra-indicated. An updated list of clinically important drug interactions is in the RCT Quick Guide (Appendix 5). This includes women taking hormonal contraceptives who will not take alternative contraception.

5. History of allergy/hypersensitivity to Isoniazid or to Rifampin, Rifabutin or Rifapentine.

6. Active TB. Patients initially suspected to have active TB can be randomized once this has been excluded.

7. Persons who have already started LTBI therapy.

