**2.11 Sample size requirements**

Our primary objective is to test whether 4RIF has superior effectiveness compared to 9INH in reducing occurrence of confirmed active TB, based on a planned intention to treat analysis. The number required depends upon the estimated rate of active TB in treated, and untreated patients, and the expected completion rates with 9INH. The expected rate of TB is hard to predict, since we will enrol patients at a wide range of increased risk. In the international sites, where most patients will be contacts (risk over 2 years of 3% 62 174 up to 8-10% 63, 175), or HIV infected (**annual** risk 3-8% 20, 21), cumulative incidence if untreated (or non-compliant) should exceed 5%, but may be only 2% in untreated subjects in Canada. Hence we assume an average cumulative incidence of 3% among untreated. Based on the assumption that 9INH has 90% efficacy if completed 140, but only 50% completion rate 70, 93, 96-102, and 4IRF efficacy is 90% the required sample size, calculated using Poisson distribution, would be 2,898 participants with full follow-up in each group (see Table S1 below). If re-calculated using the binomial distribution (and [*http://stat.ubc.ca/~rollin/stats/ssize/b2.html*](http://stat.ubc.ca/~rollin/stats/ssize/b2.html)) the sample size required would be 2% to 5% larger. Smaller differences in completion will reduce power, but higher event rates (that are certainly plausible) will substantially increase power.

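### The rule for acquired rifampin resistance (difference in resistance prevalence among TB cases) is expected to be positive even when no resistance is acquired

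*Protocol*

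**What the plan says.** Section 2.18.4 first separates two sources of resistant TB after therapy: selection during treatment (acquired) and infection with an already resistant strain (primary). It then sets the comparison: "We will compare the prevalence of resistance to INH and RIF among study participants who develop active TB". The denominator is therefore TB cases, not participants randomised.

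Each arm supplies the baseline for the other arm's drug. For INH, "The prevalence of underlying (or primary) INH resistance in the community will be assumed as the prevalence in those who took 4RIF"; for RIF, the 9INH arm plays that part. For RIF the section goes on to fix an estimator: "Acquired RIF resistance will be taken as the difference in prevalence of RIF resistance between subjects on 4RIF and 9INH". No matching difference formula is written for INH. The section closes by acknowledging limited power and calling the result descriptive.

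Two other places bear on the rule. Section 1.6 says that "Initial or primary drug resistance can render LTBI therapy ineffective". Table S1 in section 2.11 expects 4RIF to prevent 72% of cases and 9INH 45%.

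**The concern.** TB cases are themselves an outcome of treatment, so randomisation does not make the two groups of cases comparable. On the protocol's own premises, 4RIF removes mainly RIF-susceptible cases and leaves cases from strains that were RIF-resistant at infection. The resistant share among the remaining 4RIF cases then rises without any selection during therapy, and it rises further the better 4RIF works. The stated rule cannot separate this enrichment from acquisition, although the section opens by distinguishing the two.

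The exclusion of "Patients who were contacts of TB cases known to be resistant to INH, RIF, or both" does not remove the problem, because unrecognised primary resistance remains among those enrolled.

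At stake is a named secondary objective (section 1.2, objective v). A causal label would be attached to a quantity that is biased against the experimental arm, and a reader would take one or two cases of primary origin as resistance produced by rifampin.

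**Working it through.** **Inputs from the protocol.** Section 2.11: "Hence we assume an average cumulative incidence of 3% among untreated". Table S1, lower block: effectiveness 45% (9INH) and 72% (4RIF), cumulative incidence 1.65% and 0.84%, 2,898 per group at 80% power, two-sided alpha 0.05.

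**Assumptions.** The text gives no primary resistance rate; it says only that "rates of RIF resistance rates are very low and much lower than INH resistance in all participating countries" and points to an appendix table that is not shown. I take primary RIF resistance r_R at 0.5%, 1% and 2%, and primary INH resistance r_I at 10% (varied from 5% to 15%). The share m of RIF-resistant strains that are also INH-resistant runs from 0 to 1. Each drug gives no protection against strains resistant to it, the plan's effectiveness applies to susceptible strains, and true acquisition is zero. A valid measure of acquisition should return 0.

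**Plan's figure reproduced.** The square-root Poisson formula gives n = (1.960 + 0.842)² / [2(√0.0165 − √0.0084)²] = 2,897.8, or 2,898 as stated. Expected cases per group are 2,898 × 0.0165 = 47.8 on 9INH and 2,898 × 0.0084 = 24.3 on 4RIF. Untreated, they would be 2,898 × 0.03 = 86.9.

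**Simplest case (no INH resistance, r_R = 1%).** On 4RIF the resistant share is 0.01 / (0.01 + 0.99 × 0.28) = 3.48%, or 0.87 of 25.0 cases. On 9INH it is 1.00%, or 0.48 of 47.8. The rule reports 2.5 points of acquired resistance.

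**Allowing for INH resistance and co-resistance.** Per case expected without treatment:

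- 4RIF: RIF-resistant = r_R; all cases = r_R + (1 − r_R) × 0.28
- 9INH: RIF-resistant = m·r_R + (1 − m)·r_R × 0.55; all cases = r_I + (1 − r_I) × 0.55

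With r_I = 10%, the 9INH total is 0.10 + 0.90 × 0.55 = 0.595.

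| r_R | 4RIF share | 9INH share, m = 0 | 9INH share, m = 1 | False difference (points) | RIF-resistant cases expected on 4RIF |
|---|---|---|---|---|---|
| 0.5% | 0.005/0.2836 = 1.76% | 0.46% | 0.84% | +0.9 to +1.3 | 0.43 |
| 1% | 0.010/0.2872 = 3.48% | 0.92% | 1.68% | +1.8 to +2.6 | 0.87 |
| 2% | 0.020/0.2944 = 6.79% | 1.85% | 3.36% | +3.4 to +4.9 | 1.74 |

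Letting r_I run from 5% to 15% widens the ranges only to 0.9–1.3, 1.7–2.6 and 3.3–5.0 points.

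**Check on the cause.** If neither drug prevented any case, both arms would show r_R and the difference would be 0. At m = 1 the expected number of RIF-resistant cases is the same in both arms (0.87 each at r_R = 1%), and the whole difference comes from the unequal case totals (25.0 and 51.7).

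**INH.** With r_I = 10% and r_R = 1%, the INH-resistant share is 0.10/0.595 = 16.8% on 9INH. On 4RIF it is [m·r_R + (r_I − m·r_R) × 0.28] / 0.2872, that is 9.7% (m = 0) to 12.3% (m = 1). Subtracting the 4RIF baseline would give a false +4.6 to +7.1 points. With r_I = r_R = 5% and m = 1 the sign reverses, to −7.1 points, because 4RIF then enriches INH resistance too.

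**Would a new denominator be enough?** Per 10,000 randomised, with r_R = 1% and r_I = 10%, the difference without acquisition is 0 to 1.35 for RIF and about 19 to 22 for INH. The denominator alone does not turn the comparison into a measure of acquisition.

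**The case against.** The strongest reply is that the consequence is slight. The objective is to describe, the section concedes low power, and no test, stopping rule or decision depends on the result. Primary RIF resistance is said to be very low, which favours the smaller scenarios. Protection against resistant strains may be reduced and not nil, since section 1.6 says only that resistance *can* defeat therapy. All of this stands and limits the size. It does not rescue the estimator: the protocol's caveat concerns precision, whereas the fault is bias, which more cases would not remove.

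Three stronger readings are tempting but not supported:

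- *The rule will produce a false signal.* In the simplest 1% scenario (25 and 48 cases, 3.48% against 1.00%) the chance of no resistant case on 4RIF is (1 − 0.0348)^25 = 41%. The observed difference is zero or negative in about 44% of trials, and Fisher's exact test reaches p < 0.05 in about 4% (about 13% at 2% primary resistance). This is an expected bias, usually smaller than chance variation.
- *The protocol defines acquired INH resistance the same way.* It does not write that formula. It only fixes the 4RIF arm as the INH baseline, which invites the same subtraction, with an error whose size and sign depend on co-resistance.
- *Resistance is the protocol's main safety concern.* Section 1.6 ranks hepatitis first and raises resistance chiefly for unrecognised active TB at enrolment.

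**Conclusion.** Wrong as written, for RIF. On the protocol's own premises, the stated difference is expected to be above zero when nothing is acquired: roughly 1 point at 0.5% primary RIF resistance, about 2 at 1% and about 3 to 5 at 2%. The direction held in every scenario tried. It requires that some primary RIF resistance exists and that 4RIF prevents susceptible disease better than resistant disease. The size rests on assumed resistance levels, zero protection against resistant strains and the plan's 72% and 45%.

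The practical weight is moderate. The bias corresponds to a fraction of a case at the lower resistance levels, the analysis is descriptive and the primary comparison is untouched. The point should be corrected because the label is causal and the error always runs against 4RIF.

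**What to change.** In section 2.18.4, delete the sentence that equates the prevalence difference with acquired RIF resistance. Report RIF-resistant and INH-resistant TB cases per person randomised (or per 1,000 person-years) by arm, with exact confidence intervals, described as the net effect of each regimen on resistant TB and not as acquired resistance. That description is needed because the rate per person randomised also differs without acquisition, most clearly for INH.

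If prevalence among cases is still shown, call it excess resistance among cases. State that it is expected to differ between arms without acquisition, because therapy selectively prevents susceptible disease. Add that the 4RIF arm is not a clean baseline for primary INH resistance when strains are resistant to both drugs.

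The same susceptibility results serve, so the cost is wording only. The downside is that the trial no longer claims a direct estimate of acquired resistance, which these data cannot provide.

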**2.18.5 Cost-effectiveness of the two regimens**

We will have detailed information on all health system activities – including scheduled visits, therapy and tests as part of routine follow-up, unscheduled visits, tests and therapy for adverse events, and diagnostic and therapeutic activities for the cases of active TB that develop. These will be valuated using local costs for all such activities (for details see RCT Appendix 4). We will also have measured incidence of active TB among subjects randomized to the two LTBI regimens. If one arm is cheaper and associated with fewer TB cases then it will be clearly preferable from a cost-effectiveness standpoint. If one arm is more expensive but associated with fewer TB cases then we will calculate the incremental cost per additional TB case prevented by the more effective (but more expensive) regimen. In primary analysis we will use average Canadian costs to valuate all health care activities, but in secondary analyses will perform the same analyses using costs from each site. This will be of particular interest in lower-income countries, where LTBI therapy is considered a low priority 158, 199. In sensitivity analyses we will vary the costs for active TB, given that the cases detected in this study will likely be at an early stage, so may underestimate average costs. We will also vary the costs of rifampin, which is extraordinarily expensive in Canada, compared to international prices126.

**2.19 Results from Phase 1 and Phase 2**

Six years ago, we initiated a series of studies to evaluate 4RIF as therapy for LTBI. We felt the first essential requirement for 4RIF was that compliance and treatment completion had to be better than with 9INH. Hence these were primary end-points of the first study (Phase 1). Of 116 patients randomized equally to 4RIF or 9INH, 91% completed 4RIF with good compliance compared to 70% of those randomized to 9INH (p<0.001)131 200 (See Research Module Appendix: Reprints).

The experience in 2000-2001 with 2RIF-PZA mandated a careful assessment of safety, conducted in Phase 2 - a multi-centre study primarily to compare serious adverse events (SAE) with 4RIF and 9INH. Consenting patients were randomized in equal numbers to 4RIF or 9INH using a web-based patient registration and randomization developed by [name] of the University of Sherbrooke. *To view the registration, randomization, and SAE reporting web-site, use Internet explorer (at least 6.0) to go to:* [http://tbera-demo.crc.chus.qc.ca](http://tbera-demo.crc.chus.qc.ca/)*. Username:* **[name]***, password:* **review***; domain:* **rsr** *(until Feb 1 2009). Enter these once when prompted, and then enter the same username and password a second time, when prompted again. This gives administrator rights to view a demonstration database, with fictitious patients.* Randomization was stratified by site in blocks of variable size. Investigators performed a standardized evaluation for each possible SAE. If the study drug was permanently discontinued, all clinical, lab, and follow-up information was reviewed independently by a three member panel, blinded to the study drug, to judge the type, severity and likely relationship to the study drug (Appendix 4).

We experienced more difficulties recruiting patients than anticipated at several Canadian sites. In the first year we intensified training and supervision, and opened a new sub-site. When this was not enough, investigator and CIHR approval was sought to shift budget allocations from low enrolling sites to start two new international sites – in Brazil and Saudi Arabia, ***within the originally awarded total budget***. Enrolment at all sites subsequently increased to average 40 patients per month. We had planned a sample size of 549 per arm to provide 80% power (2 sided test) to demonstrate a significant difference in SAE rate if the true rate with 9INH was 4% and 4RIF was 9%, or was 5% with 9INH and 2% with 4RIF. After 25%, 50% and 75% of planned enrolment, the DSMB reviewed interim analyses – still blinded to the study drugs. In January 2007, the 3rd interim analysis revealed that SAE were significantly fewer in one arm. The DSMB asked to be unblinded, and when they learned that 4RIF had the lower rate of SAE, they recommended discontinuation of enrolment. Of 420 subjects randomized to 4RIF, 7 developed Grade 3-4 adverse events attributed to study therapy by the independent panel, compared to 17 of the 427 on 9INH (Risk difference (4RIF-9INH): -2.3%; [95% Confidence interval: -0.1% to -5%] p=.04). Grade 3-4 hepatitis occurred in 3 taking 4RIF, compared to 16 who started 9INH (-3.1%; [-1% to -5%], p=.003). Grade 1 or 2 adverse events attributed to study drugs were similar in the two arms. Asymptomatic reduction in platelet count and white blood count were significantly more frequent during treatment with 4RIF. Completion rates were 78% with 4RIF and 60% with 9INH (Risk difference: 18% [12% to 24%], p<.001) 148. Average health system costs were significantly lower with 4RIF. Incremental cost effectiveness analysis revealed that 4RIF would be cost saving and prevent more cases if efficacy was at least 75%, and would be cost saving if efficacy is more than 65% 147.

We believe that a study to assess effectiveness of 4RIF is now justified. This regimen has been demonstrated to have better completion, lower costs, and is safer than 9INH, particularly for hepatotoxicity - the most important and potentially lethal adverse event of INH therapy (and of 2RIF-PZA). In Phase 2, 847 subjects were enrolled, randomized, treated and followed to detect active TB - using the methods proposed here, making the present proposal more cost-effective.

**SECTION 3 TRIAL MANAGEMENT**

**3.1 Day to day running** (See also RCT Appendix 7 - Time-Table)

This is described in Sections 2.3 (recruitment), 2.7 (follow-up/data gathering), and 2.8-2.9 (measuring outcomes).

**3.2 Role of applicants**

[name] will chair the trial steering committee, supervise the central coordinating staff, liaison with site PI’s, and take primary responsibility for overall data analysis and report writing. Each site PI will supervise all aspects of site trial management (ethics, recruitment, and follow-up), and site-specific staff. To take advantage of members’ expertise, added specific responsibilities will be assigned as described in detail in RCT Appendix 6.

**3.3 Trial steering committee, DSMB, and Clinical review panel**

The trial steering committee will consist of the PI, site investigators, and study manager ([name]). They will meet by telephone conference every 3 months in the first year, and then every 6 months, to review recruitment, randomization, operational issues, and DSMB reports. This committee will decide on early termination (if recommended by the DSMB), major protocol and/or consent modifications, and budget re-allocations. The membership, responsibilities, and functioning of the DSMB are described in Section 2.9.3, and of the clinical review panel in Section 2.9.1.
